### Eligibility criteria

The study population consists of adult patients (> 18 years old) that are approved for cochlear implantation according to standard care criteria. Patients will initially undergo a series of diagnostic tests to assess eligibility for cochlear implantation. These are as follows: a CT scan, a pure tone audiogram/speech test, psychological evaluation, and a consultation by the audiologist and ENT specialist. The Cochlear Implant Team of the UMC Utrecht will assess the work-up results and assess eligibility for cochlear implantation, according to the current clinically applied criteria.

All cochlear implant models will be included in this study. The choice for the cochlear implant model lies with the patient and the CI team of the UMC Utrecht and will not be affected by taking part in this trial. In order to be eligible to participate in this study, a participant must have provided written informed consent authorization before participating in the study. They also must have Dutch written language proficiency and be physically able to undergo a CBCT scan.

A potential participant who is a revision or reimplantation candidate, is unable to understand or sign informed consent, or is pregnant during the trial will be excluded from participation in this study.

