### Sample size

This sample size calculation was based on the primary outcome, R/S migration after 12 months. Due to limited quality evidence on the migration rate for both techniques, an estimation of the migration rates cannot be based on literature; therefore, we base our assumptions on clinical expertise [34, 42, 43]. We consider a migration under 1.0 mm or 1° to be clinically irrelevant. Migration under these cut-off points is within the measurement error margin of the measurement technique of the CBCT scan analysis. A sample size of 51 per study arm reaches 80% power (*β* = 0.8) and a significance level (*α*) of 0.05 with a non-inferiority margin of 1.0 mm. Standard deviation is estimated at 2.0 mm based on the database of Maxwell et al. [43]. In order to cover for possible loss to follow-up estimated at a maximum of 10%, we will include 56 patients per study arm.

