### Randomization and blinding

Patients will be randomly assigned to one of the two study groups with 56 patients allocated in each group. Randomization takes place in the UMC Utrecht-endorsed electronic data capture system Castor EDC. (https://www.castoredc.com/). After giving informed consent, patients will be randomized with an allocation ratio of 1:1 and variable block sizes, with stratification for age (18–50 years, >50 years). Stratification is applied in both study groups. This is a single-blind study, meaning that only participants are blinded for the treatment allocation. The randomization will be done before surgery and patients will not be informed about the allocation. The research team is not blinded. The outcome data will be blindly analyzed. Blinding of the data will be performed by the electronic Case Report Form system used (see section “Data collection plan”). In the event that a revision surgery is necessary for removal or repositioning of the CI, unblinding is permitted. A member of the research team will inform the subject of the allocation.

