#### Statistical analysis secondary objectives

COMPASS questionnaire scores between intervention and control at 3 and 12 months after cochlear implantation will be calculated using the unpaired *t*-test (or the Mann-Whitney *U* test).

Statistical analysis of electrode migration data will be compared in a number of cases and percentages. To calculate any association between electrode migration of ≥ 1 mm and R/S device migration, and between electrode migration and a decrease in speech performance tests, Pearson’s correlation test or a Spearman rank correlation test will be performed. Electrode impedance values will be compared between the groups with the unpaired *t*-test (or the Mann-Whitney *U* test). CVC word score tests (with and without noise) will be compared between the groups with the unpaired *t*-test. Within-group comparisons will be calculated with differences of mean values. A clinically relevant speech performance decrease is a speech performance test score decrease of ≥ 7% when scoring between 30 and 80%, and ≥ 5% when the patients’ scores < 30 or > 80% on the speech performance test, a definition based on clinical experts. Incidence and degree of complications will be reported by means of frequencies.

Participants who withdraw from the study prematurely will be considered lost and will be replaced. Reasons for withdrawal or premature termination will be documented. Potential missing data will be handled using multiple imputation. Complete case analyses will be performed as a sensitivity analysis. All analyses will be performed on an intention-to-treat basis.

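### The rule that withdrawn participants are replaced cannot be squared with intention-to-treat, multiple imputation and the fixed 56 per arm, and it leaves unclear who enters the primary analysis

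*Protocol article*

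**What the plan says.** The last paragraph of the protocol article's section on statistical analysis of the secondary objectives sets four rules:

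- Withdrawal: "Participants who withdraw from the study prematurely will be considered lost and will be replaced".
- Missing data: "Potential missing data will be handled using multiple imputation".
- Sensitivity: "Complete case analyses will be performed as a sensitivity analysis".
- Principle: "All analyses will be performed on an intention-to-treat basis". The Abstract and the general Statistical analysis section also commit to intention-to-treat.

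Two other sections bear on the same patients. Sample size states: "A sample size of 51 per study arm reaches 80% power", and then "In order to cover for possible loss to follow-up estimated at a maximum of 10%, we will include 56 patients per study arm". Randomization and blinding fixes the number: "Patients will be randomly assigned to one of the two study groups with 56 patients allocated in each group".

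The article does not say whether a replaced participant stays in the analysis set, or how replacement fits with a total of 112.

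**The concern.** These rules settle who is in the primary analysis, and they do not fit together. Considered lost and replaced, read naturally, means that the withdrawn patient leaves the data set and a new one fills the place. Intention-to-treat and imputation say that the withdrawn patient stays.

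This matters more than usual here for two reasons. First, Background and rationale says that migration of the receiver/stimulator can bring pain, device problems, device failure and sometimes revision. Interventions: modifications names device failure and persisting pain among the reasons for revision, in which the implant would be removed. Early exit may therefore be related to the primary outcome. Second, this is a non-inferiority trial. If patients whose device moved drop out of the tight-pocket analysis, that arm looks closer to the bony-recess arm, which helps the claim. Randomisation precedes surgery and the research team is not blinded, so those who record withdrawals and enrol replacements may know the arm.

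**Working it through.** **1. The plan's own sample size.** Inputs from Sample size: margin 1.0 mm, SD 2.0 mm, power 80%, alpha 0.05. The sidedness of alpha is not stated. I assume a true difference of 0 and one-sided 0.05, because that reproduces the stated figure.

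- Normal approximation: n per arm = 2 x (1.645 + 0.842)² x 2.0² / 1.0² = 49.5, so 50.
- Exact t calculation: power is 79.9% at 50 per arm and 80.6% at 51, so 51 as stated. One-sided 0.025 would need 64.
- Allowance for 10% loss: 51 / 0.9 = 56.7, so 57. The stated 56 is one short, which is immaterial.

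**2. Is replacement needed for power?** With 56 per arm and the maximum 10% loss, 56 x 0.9 = 50.4 per arm remain, with power of about 80% (79.9% at 50, 80.6% at 51). The allowance already does the job.

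**3. What replacement adds.** At 10% loss, 112 x 0.10 = 11.2 patients withdraw. Replacing each once gives about 112 + 11 = 123 randomised. If replacements are lost at the same rate, 112 completers need 112 / 0.9 = 124.4, so 125. Power with 56 completers per arm is 83.8%. The same loss is covered twice, and the allocation is no longer 56 per group.

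**4. The two readings side by side.**

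| Reading | Intention-to-treat and imputation | 56 per arm, 10% allowance |
|---|---|---|
| Withdrawn patient leaves the analysis, replacement enters | Broken | 56 analysed, but more than 56 randomised |
| Withdrawn patient stays and is imputed, replacement added | Kept | Exceeded; loss covered twice |

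Neither reading satisfies every stated rule.

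**5. Possible size of bias if withdrawn patients are left out.** The documents give no withdrawal rate by migration status, so all inputs here are assumptions. Let a share q = 0.20 of pocket devices shift L = 5 mm, the rest and all controls not at all. The true excess is 0.20 x 5 = 1.0 mm, equal to the margin. Let a share w of the movers leave the analysis and nobody else.

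- No replacement: mover share = q(1 - w) / (1 - qw). For w = 0.25: 0.15 / 0.95 = 0.158, excess 0.79 mm. For w = 0.50: 0.10 / 0.90 = 0.111, excess 0.56 mm.
- One replacement per withdrawal, same risk, followed to 12 months: mover share = q(1 - w) + q²w. For w = 0.25: 0.15 + 0.01 = 0.16, excess 0.80 mm. For w = 0.50: 0.10 + 0.02 = 0.12, excess 0.60 mm.

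So a true 1.0 mm appears as about 0.8 or 0.6 mm either way. The withdrawals amount to qw = 5% or 10% of the pocket arm.

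A wider range: if 5% to 10% of the arm is left out and those patients moved 2 to 6 mm more than the rest, the arm mean falls by share x excess, from 0.05 x 2 = 0.1 mm to 0.10 x 6 = 0.6 mm. That is 10% to 60% of the margin.

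**The case against.** The strongest defence is that the article never says withdrawn patients leave the analysis. It commits to intention-to-treat in three places and makes complete-case analysis only a sensitivity analysis. One can therefore read it as keeping and imputing withdrawn patients while recruiting extra ones. On that reading replacement is redundant but does not break intention-to-treat. This stands as far as it goes, and it is why the finding is an unreconciled rule and not a proven exclusion. It does not rescue the text, because that reading overruns the 56 per group and the loss allowance.

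A full protocol or analysis plan might define the analysis sets. That is fair, but the replacement rule is stated here and conflicts with what is stated here.

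A reader might infer that replacement itself creates the bias. It does not: step 5 shows slightly less distortion with one-for-one replacement than with plain loss. The cause is leaving outcome-related withdrawals out. Replacement only makes the resulting data set look complete.

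A reader might also infer that patients with migrated devices will be removed. The documents do not say so. Revision is described as rare, nothing equates it with withdrawal, and follow-up coincides with routine rehabilitation visits. Some withdrawals may also occur before surgery, when there is no device to move.

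Finally, Eligibility criteria says that a person who "is pregnant during the trial will be excluded from participation in this study". A reader might take this as a post-randomisation exclusion. Its subject is a potential participant and it stands among the eligibility criteria; nothing there removes a randomised patient from the analysis. It is not part of this point.

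**Conclusion.** The point holds. The replacement rule, intention-to-treat with multiple imputation, and the fixed 56 per arm with its 10% allowance cannot all be followed as written. Replacement is not needed for power: the allowance leaves about 50 patients per arm and about 80% power, assuming one-sided 0.05 and loss no greater than the stated maximum.

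The consequence for bias is possible and not shown. If withdrawn patients are left out, and if withdrawal is related to migration in the pocket arm, the result moves towards non-inferiority. The illustration of 1.0 mm appearing as about 0.8 or 0.6 mm rests on inputs that the documents do not give, and on the one-sided assumption that only patients whose pocket device moved leave. The 0.6 mm case makes the pocket arm's whole 10% loss consist of such patients. The true size is unknown. Since the rule decides who is analysed for the primary outcome and the remedy is wording, it should be settled before analysis.

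**What to change.** - Delete the replacement rule, or limit it to participants who leave before surgery.
- State that every randomised and operated participant stays in the intention-to-treat primary analysis under the multiple imputation already planned. Deleting the replacement sentence without this statement would not remove the possible bias.
- Include the 3-month CBCT result and the scheduled tape measurements (1, 4 and 8 weeks, 3 and 12 months) in the imputation model.
- Rely on the 56 per arm to cover loss.
- For patients revised before 12 months, use migration data observed after baseline and before revision where they exist. Do not carry the baseline scan forward as zero migration. CBCT is scheduled only within 48 hours, at 3 months and at 12 months, so for anyone revised before the 3-month scan the last scheduled scan is the baseline one, and carrying it forward would record no movement in the very patients of concern.

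The cost is a few sentences, with no added visits or scans, and slightly fewer complete cases than with replacement.

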#### Data management

Trial quality will be monitored independently by a local monitor (UMC Utrecht) once a year. The local monitor will check 10% of signed ICs, inclusion and exclusion criteria, source data, and serious adverse events (SAE). From the first three participants, the inclusion and exclusion criteria will also be checked. The study does not have a public involvement group [29].

### Harms

The investigator will submit a summary of the progress of the trial to the accredited MREC once a year. Information will be provided on the date of inclusion of the first participant, numbers of participants included and numbers of participants that have completed the trial, serious adverse events (SAEs)/serious adverse reactions, other problems, and amendments.

### Ethics and dissemination

The results (positive or negative) of this study will be disclosed unreservedly. Data and results of research are owned by the investigators. The results of the research will be submitted for publication in peer-reviewed scientific journals. Disputes on the interpretation of the results may not lead to an unnecessary delay in publication. None of the parties concerned has a right of veto. In addition, trial results will be communicated via symposia and relevant conferences on otology and cochlear implantation. Results will be summarized for the general public and interested trial participants and shared on the sponsor’s website.

The sponsor has an insurance which is in accordance with the legal requirements in the Netherlands (Article 7 WMO). This insurance provides cover for damage to research subjects through injury or death caused by the study. The insurance applies to the damage that becomes apparent during the study or within 4 years after the end of the study.

## Discussion

Cochlear implantation by means of creating a tight subperiosteal pocket without drilling a bony seat is a minimally invasive fixation technique with many advantages. However, the safety of this technique has not yet been proven with certainty. The objective of this study is the comparison of two broadly used surgical techniques for the fixation of the receiver/stimulator device during cochlear implantation, with and without drilling. This is the first randomized controlled trial that directly compares the minimally invasive technique with the conventional method of drilling a bony seat. Multiple outcomes will be assessed, using objective measures for the assessment of R/S device and electrode array migration, speech performance, and patient experience. A limitation of this trial is the monocenter design, which may affect recruitment rate and external validity.

## Trial status

Protocol version 2, 20-01-2022. The trial is currently in the recruitment phase. The first patient was recruited on 27 October 2021. Thirteen of 112 patients were included in the study on 11 May 2022. Approximate date of trial completion: 27-10-2023.

## Data Availability

Only research members directly involved in this study and the monitor of the study will get access to all of the collected research data. Any data required to support the protocol can be supplied on request. Data sharing including the participant dataset, full protocol, and statistical codes will be considered upon reasonable request.

## Abbreviations

3D: Three-dimensional
AE: Adverse event
CBCT: Cone-beam computed tomography
CI: Cochlear implant
COMPASS: Cochlear implant awareness questionnaire
CVC: Consonant-vowel nucleus-consonant, Dutch speech perception test
ENT: Ear, nose and throat
IC: Informed consent
ICP: Iterative Closest Point
IRB: Institutional Review Board
MERC: Medical research ethics committee (MREC); in Dutch: medisch ethische toetsing commissie (METC)
R/S: Receiver/stimulator device
WMO: Medical Research Involving Human Participants Act; in Dutch: Wet Medisch-wetenschappelijk Onderzoek met Mensen
